### The nutritional support team

The NST was composed of one paediatrician specialised in gastroenterology and clinical nutrition as well as two dieticians. This team was created one year prior to study implementation. The team usually intervenes at the request of the clinical teams in order to confirm the diagnosis of malnutrition in cases of doubt, to coordinate nutritional care and provide relevant advice, and if necessary to prescribe nutritional support (oral nutritional supplement, enteral or parenteral nutrition).

### Intervention

The implementation of our multifaceted intervention was coordinated by the NST and pertains to the cluster level. It had three major components: a) access to a computerised malnutrition screening system and automatic alert system, b) an awareness campaign directed toward the health care workers and c) a leadership based strategy (see Figure 1).

**Figure 1 F1:**
[figure not shown]
**The multifaceted intervention. **This figure presents the different components of the multifaceted intervention, as well as the professionals (target groups) and the relevant stages of nutritional treatment. NST: Nutritional Support Team.

#### Computerised tools

A computerised malnutrition screening system was made feasible through the nurses’ measurement of child’s height and weight at admission and the collection of these data in the IT system. Using this information in addition to the child's age and sex, the Algoped algorithm ran automatically, alerting physicians about the nutritional status of every child at the time when drugs were prescribed electronically. The message appeared in real time when the physician sought to prescribe a treatment, indicating “moderate malnutrition” or “severe malnutrition” based on the automatic calculation of the nutritional status of the child, in accordance with the calculation instructions of the Algoped algorithm:

– In the absence of malnutrition, no message appeared;

– In case of moderate malnutrition, the message indicated that the prescribing physician should make contact with the department dietician in order to decide what measures to take;

– In case of severe malnutrition, the message indicated that the prescribing physician should make contact with the NST in order to decide what kind of nutritional support to perform.

This algorithm was intended to facilitate the coordination of the treatment of malnutrition among members of the medical teams, the dieticians and the NST.

In addition, a monitoring dashboard was updated daily, providing the dieticians with the list of malnourished children in their department and allowing them to intervene independently of clinicians’ calls. The NST also had access to this dashboard.

#### Awareness campaign for health care workers

This awareness campaign consisted of 3 approaches: educational symposiums, training sessions and regular outreach visits to the various departments with the aim of informing health care workers about the frequency and severity of malnutrition among hospitalised children. Each approach was adapted to a specific professional category (physicians, dieticians, nurses and auxiliary nurses). In particular, the message aimed at nurses focused on appropriate screening, which requires systematic weight and height measurements. On the other hand, physicians and dieticians were made aware of evidence based care with which to comply, once they had been alerted about the child’s malnutrition status through the IT system. As well, the teams were trained to refer to the NST as appropriate, namely based on the degree of severity of the malnutrition observed.

In addition to this awareness campaign, case reviews were given by the NST during the initial months of the intervention in the various departments of the intervention arm (two case reviews per department). During these case reviews, the NST presented the files of malnourished children treated in the department where the review session was held. These case reviews involved the participation of physicians, dieticians, nurses and auxiliaries nurses.

#### Leadership based strategy

A leadership oriented strategy focused mainly on increasing the sensitivity of the computerised malnutrition screening system. To this end, the medical and nursing advisory boards of the hospital established the mandatory measurement of the weight and height of each hospitalised child, as well as the mandatory entry of these data into the IT system. In terms of intervention, the medical heads and nursing coordinators of each department were in charge of ensuring compliance with this recommendation. In addition, the NST was responsible for coordinating the dieticians across the hospital and for leading a periodic multidisciplinary meeting in order to analyse clinical incidents related to nutritional care and to facilitate the sharing of experience among attendees from various medical specialties.

### Nutritional support policy

Nutritional support provided by the department dietician and/or by the NST depended on the seriousness of nutritional status, the functionality of the digestive tract, the causal pathology and the prognosis. In case of moderate or severe malnutrition, daily weighing and investigation of malnutrition etiology were prescribed respectively by the department dietician or by the NST. Physiotherapy was prescribed when appropriate. Moreover, in cases of severe malnutrition, nutritional support was initiated as soon as possible, using the enteral or parenteral route, or both, according to the judgment of the NST.

### The control group

In the control arm, no specific intervention was implemented to improve the management of malnutrition (*i.e.*, with no access to the computerised malnutrition screening system, no educational campaign and no leadership based strategy) and the teams provided care as usual. In addition, as usual, the NST could be called for counselling at any time within the control arm.

### Outcomes and measurements

Primary outcomes were chosen for their ability to assess the quality of care within each cluster based on health care workers’ adherence to recommended practices for every malnourished child; they included the number of daily weighings during hospitalisation (total number of weighings divided by length of stay), the investigation of malnutrition etiology (a detailed analysis of malnutrition causes is present in the medical record) and the management of malnutrition by a dietician and/or the NST.

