**Population at patient level**	
*Inclusion criteria*	Age 1 month to 18 years old
	Children recorded as malnourished based on their weight/height and height/age ratios upon hospital entrance, according to the Algoped nutritional risk score
*Exclusion criteria*	Age under one month, liver or kidney abnormalities, severe heart failure
	First weight recorded more than 2 days after admission, first height recorded more than 15 days after admission
	Stay less than 2 days

Head physicians of all eligible departments were contacted and invited to participate. All medical and surgical departments providing acute care in this paediatric university hospital participated in the trial (*i.e.*, 8 departments, 393 acute care beds (207 in medicine and 59 in surgery) performing 29 518 stays a year) except neonatal, intensive care and emergency units. Approximately 300 professionals were targeted (55 physicians and medical residents, 115 nurses, 12 dieticians, 100 paediatric auxiliary nurses and 27 physiotherapists).

Some nursing teams work across several departments. As a consequence, because our intervention targeted the practices of health care professionals, we grouped the relevant departments together into clusters in order to minimise contamination bias between departments. A total of six clusters were determined.

According to the French paediatric guidelines for the screening and treatment of malnutrition, the Algoped nutritional risk score was employed for assessing the nutritional status of every child based on weight and height measured at admission by health care workers [11]. Detection of malnourished children was based on the combined interpretation of two ratios. First, in order to detect acute malnutrition (stunting), the weight/height ratio (W/H) was calculated by dividing the child’s observed weight by the expected weight related to their observed height [14]. Second, in order to detect chronic malnutrition (wasting), the height/age ratio (H/A) was calculated by dividing the child’s observed height by the expected height related to their age. In cases of W/H > 90% and/or H/A > 94%, there was considered to be no malnutrition in the patient. In cases of W/H 80-90% and/or H/A 85-94%, there was moderate malnutrition, while W/H < 80% and/or H/A < 85% indicated severe malnutrition [15,16].

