### Data analysis of the cluster randomised trial

All statistical analyses will be performed in Statistical Analysis System (SAS®) software version 9.2 (SAS Institute, Cary, NC). Analyses will be performed according to the intention-to-treat principle. All malnourished children screened in all clusters allocated to the intervention or control arm will be included in the analysis. In the event of multiple hospitalisations for the same patient, only the first stay of the study period will be retained.

Baseline characteristics will be summarised by pre- and post-intervention period and treatment group using frequency (percentage) for categorical variables and means (standard deviation) for continuous variables.

Clustering will be taken into account: a generalized estimated equations (GEE) approach will be used to analyse the impact of the multifaceted intervention on primary and secondary outcomes [20]. A GEE Poisson regression model will be performed for count data (as number of daily weighings) and GEE logistic regression models for binary variables (as investigation of malnutrition etiology, management by dietician, nutritional supplementation, complication occurrence during hospitalisation). The paediatric departments will be entered as the clustering variable into each model. For the GEE Poisson, the length of stay will be used as an offset. An exchangeable correlation matrix will be specified to account for potential within-cluster homogeneity in outcomes: all pairwise correlations among children within departments are the same. Robust estimates of the standard errors will be obtained which ensures, provided the model is correct, that the estimates are consistent even if the working correlation matrix is not correct. The impact of the multifaceted intervention will be adjusted for individual level characteristics included age, severity of malnutrition, comorbidities occurrence, complications occurrence and length of hospital stay after controlling for the collinearity between covariables. A Wald statistic will be used to test the significance of each coefficient in the model. The intervention effect will be expressed as adjusted odds ratio with its 95% confidence interval. GEE regression models will be fit using the SAS PROC GENMOD. Corresponding overall intra cluster correlation (ICC) coefficient was also estimated from GEE method using the CORRW option from the SAS PROC GENMOD.

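### The primary weighing outcome counts the one weighing that eligibility guarantees in both arms, so at equal stay it understates the size of a change in weighing practice

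*Protocol article*

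**What the plan says.** The section Outcomes and measurements presents the primary outcomes as measures of staff adherence to recommended care. The first is "the number of daily weighings during hospitalisation (total number of weighings divided by length of stay". It does not set the first weighing aside.

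Table 1 includes "Children recorded as malnourished based on their weight/height and height/age ratios upon hospital entrance", which requires a weight. It excludes children with "First weight recorded more than 2 days after admission, first height recorded more than 15 days after admission", and also "Stay less than 2 days".

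The practice to be measured comes later. Under Nutritional support policy, once malnutrition is identified, "daily weighing and investigation of malnutrition etiology were prescribed respectively by the department dietician or by the NST".

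The section on data analysis of the cluster randomised trial plans a GEE Poisson model for the weighing count and states: "For the GEE Poisson, the length of stay will be used as an offset". The planned adjustment set also contains "comorbidities occurrence, complications occurrence and length of hospital stay after controlling for the collinearity between covariables".

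**The concern.** The admission weighing is the screening measurement that makes a child eligible. Without an early one the child is not in the analysis, so it is present in both arms by construction and precedes the recommendation whose uptake is being assessed. A child never weighed again still scores 1/L: 0.50 for a 2-day stay, 0.25 for 4 days, 0.14 for 7 days.

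A constant added to both arms pulls the rate ratio towards 1, most strongly when stays are short. What is at stake is the reading of the result: the reported ratio would be taken as the change in weighing practice, and it would be too small.

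**Working it through.** **The plan's own figure.** The sample size is for a binary rate: 50% v 75%, two-sided alpha 0.05, power 80%, which needs 58 per arm. The design effect is 1 + (200 − 1) × 0.05 = 10.95. The total is 2 × 58 × 10.95 = 1270, which is 1.5% below the stated 1289. That figure is not in dispute and does not depend on the weighing definition.

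**Inputs from the article.** The outcome is total weighings over length of stay; each analysed child has at least one weighing; the shortest eligible stay is 2 days; length of stay is the Poisson offset.

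**Assumptions.** One guaranteed weighing, at most one weighing a day, and probability p of a weighing on each of the remaining L − 1 days. I take p = 0.50 v 0.75, a 25-point change, for illustration.

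**Formulas.**
- Expected outcome: [1 + (L − 1)p] / L
- Arm difference at equal stay: (p1 − p0)(L − 1)/L
- Rate ratio at equal stay: [1 + (L − 1)p1] / [1 + (L − 1)p0]

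A Poisson model with a log-stay offset and an arm term compares total weighings over total days, so L can be read as the mean stay.

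| L (days) | p = 0.50 | p = 0.75 | Difference | Share of 0.25 | Rate ratio (true 1.50) |
|---|---|---|---|---|---|
| 2 | 0.750 | 0.875 | 0.125 | 50% | 1.17 |
| 4 | 0.625 | 0.8125 | 0.1875 | 75% | 1.30 |
| 5 | 0.600 | 0.800 | 0.200 | 80% | 1.33 |
| 7 | 0.571 | 0.786 | 0.214 | 86% | 1.375 |
| 10 | 0.550 | 0.775 | 0.225 | 90% | 1.41 |
| 14 | 0.536 | 0.768 | 0.232 | 93% | 1.43 |

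Simulating the Poisson offset model (clustering ignored) gives the same ratios at mean stays of 4, 5, 7 and 10 days. Adding stay as a covariate leaves them unchanged.

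**Other baselines, 25-point gain, L = 4.** For 0.20 to 0.45: 2.35/1.60 = 1.47 against a true 2.25. For 0.70 to 0.95: 3.85/3.10 = 1.24 against a true 1.36.

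**Without the guaranteed weighing.** (Weighings − 1)/(L − 1) has expectation p, so the ratio is 0.75/0.50 = 1.50 at every L.

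**Unequal stay, identical practice.** Mean stay 5 v 4 days: at p = 0.5, 0.600 v 0.625, a false ratio of 1.04; at p = 0.2, 0.36 v 0.40, a false ratio of 1.11. These hold with the offset alone. With stay also entered as a linear covariate, simulation (assumed geometric-type stays, clustering ignored) gives about 1.00 to 1.01.

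**Repeat weighings on one day.** A 7-day stay weighed twice on three days and once on a fourth scores 7/7 = 1.0, with 4/7 = 0.57 of its days covered.

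**The case against.** **The test is hardly affected.** This stands. At equal stay the guaranteed weighing adds the same constant to both arms, so the difference in counts and its variability stay almost as they were. The attenuation is towards no effect.

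**The size is assumed, and the short-stay rows are extreme.** This also stands. The loss in the absolute difference is about 1/mean stay, so 14% at 7 days and 10% at 10. The 25-point target belongs to the binary sample-size calculation, so a smaller difference on the weighing count contradicts no stated target.

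**A reader might infer a false arm effect if stays differ.** Length of stay is a secondary outcome and may differ by arm, and the offset alone does not remove the dependence. But the planned model also includes stay as a covariate, which absorbs nearly all of it in the cases above. Whether to adjust for a variable measured after randomisation is a separate question.

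**A reader might infer that the absence of a one-per-day limit adds to the understatement.** The article does not support that. Same-day repeats can mask missed days or inflate a score in either arm, so the direction is open. A condensed article may also leave this counting rule to the full protocol, and nothing in it suggests that repeats were common.

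**Replacing the primary outcome now would look post hoc.** This stands. Data were gathered up to August 2011, analysis was under way, and researchers were not blinded. Starting the clock at the actual qualifying weighing would also leave some 2-day stays with no time at risk, and the article does not document that every weighing was dated. The remedy must respect these limits.

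**Conclusion.** The concern holds for the size of the weighing effect. The outcome contains a weighing that eligibility guarantees in both arms, and neither the offset nor the stay covariate removes the resulting dilution. Under 50% v 75% later-day weighing, a true ratio of 1.50 would be reported as about 1.30 to 1.41 for mean stays of 4 to 10 days; the loss is larger for shorter stays and small for long ones. This rests on at most one weighing a day, equal stay between arms, and assumed values for stay and baseline practice.

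It does not follow that the significance test is invalid, that differing stays would produce a material false effect under the planned model, or that the sample size is wrong.

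**What to change.** Add to Outcomes and measurements, and to the data analysis section, an analysis of weighings after the qualifying one: (total weighings − 1) as the count and log(length of stay − 1) as the offset, in the same GEE Poisson model. Because stays under 2 days are excluded, length of stay − 1 is at least 1 and the offset is defined for every eligible child. For a child first weighed later than the first day, this is a slight approximation to the days remaining.

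Keep the planned ratio and report the two side by side. Label the new analysis as additional, with its date and the statement that data collection was complete. Interpret the size of the weighing effect from it.

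Where weighing dates were extracted, also report the number of days with at least one weighing over the remaining days; this settles the same-day-repeat question. Report how many children have no remaining days under that version.

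The cost is a little more analysis work and a second estimate to report. No new data are needed for the main addition.

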#### Secondary outcome measures

*For clinical practice*: Appropriate call-in of the NST;

*For clinical impact on children*:

Incidence of complications linked to nutritional status during the hospital stay;

Evolution of nutritional status during the hospital stay;

*For economic measures*: Mean length and cost of stay.

Data concerning primary and secondary outcome measures were available at the patient level and were extracted from the medical records by an independent research team. The research team received handouts and training to become familiar with data collection. Data relative to the length of stay and the cost of treatment were obtained from the hospital’s claims databases.

The same data were gathered for the observational study and for the interventional study.

In addition, we monitored the intervention process. The research team gathered information on the availability and usage of the information technology tools, on the actions carried out by the NST in the framework of the awareness campaign for health care workers, and on the actions conducted within the leadership based strategy.

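### Entry to the analysis requires a recorded height, allowed up to day 15, so differing height timing between arms can create a difference in mean length and cost of stay with no true effect

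*Protocol article*

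**What the plan says.** - **Outcome.** The protocol article, Secondary outcome measures, names "Mean length and cost of stay" as the economic outcome. "Data relative to the length of stay and the cost of treatment were obtained" from the hospital's claims databases. No later time origin is given, so the figures appear to cover the whole stay.
- **Entry.** Table 1 includes "Children recorded as malnourished based on their weight/height and height/age ratios upon hospital entrance". Both ratios use the child's height.
- **Windows.** Table 1 excludes children with "First weight recorded more than 2 days after admission, first height recorded more than 15 days after admission", and also "Stay less than 2 days".
- **Intervention arm.** In the awareness campaign, "the message aimed at nurses focused on appropriate screening, which requires systematic weight and height measurements". Under the leadership strategy, the hospital's advisory boards "established the mandatory measurement of the weight and height of each hospitalised child", together with its entry in the IT system.
- **Control arm.** Care as usual, with "no access to the computerised malnutrition screening system, no educational campaign and no leadership based strategy".
- **Analysis.** All screened malnourished children are included. The listed adjustment variables are age, severity of malnutrition, comorbidities, complications and length of stay. Pre/post comparisons within each arm are also planned.

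**The concern.** No child can be classed as malnourished before a height exists. The 2-day minimum stay closes the gap for weight, which must be recorded within 2 days. It does not close it for height, which may come as late as day 15. Long stays give more time to be measured, so they are over-represented in the analysed set. How strongly depends on how measurement is spread over the stay.

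The intervention acts on exactly that process. Entry is therefore decided after randomisation, by something the intervention changes and that is tied to the outcome. Adjusting for age, severity or comorbidities does not undo selection on stay, and length of stay cannot serve as a covariate for itself. The pre/post comparison in the intervention arm is exposed too, because height timing may change when the intervention starts.

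What is at stake is a statement about a shorter or cheaper stay, in a trial whose Background expects such teams to bring economic savings.

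**Working it through.** The article gives no figure for length or cost of stay, so there is none to reproduce. The sample size of 1289 concerns the primary outcomes and does not bear on this point.

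**1. Formula.** Let F(l) be the probability that height is recorded by day l. If height timing is unrelated to stay L, then

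mean stay analysed = Σ L·P(L)·F(min(L,15)) / Σ P(L)·F(min(L,15)), over L ≥ 2.

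If F is flat from day 2 onward, it cancels and the analysed mean equals the true mean. If F rises after day 2, long stays are over-weighted. What matters is how steeply F rises in each arm, not how many children are measured.

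**2. Assumed inputs** (none are in the document). Stay is lognormal with median 4 days and log-SD 0.9, rounded up and kept if at least 2 days, and identical in both arms. Height is recorded on day 1 with probability h0, then with probability h per day, so F(l) = h0 + (1 − h0)(1 − (1 − h)^(l−1)).

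**3. Weight of a 15-day stay relative to a 2-day stay, F(15)/F(2).**

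| Setting | Control | Intervention |
|---|---|---|
| A: control 50% then 10% per day; intervention 90% then 20% | 0.886/0.550 = 1.61 | 0.996/0.920 = 1.08 |
| B: control 50% then 1% per day; intervention 60% then 20% | 0.566/0.505 = 1.12 | 0.982/0.680 = 1.44 |

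**4. Simulated mean stay with no true effect** (true mean about 6.85 days).

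| Setting | Control | Intervention | Difference |
|---|---|---|---|
| A, all screened | 7.68 | 6.99 | −0.69 (−9%) |
| A, height by day 2 | 6.85 | 6.86 | about 0 |
| B, all screened | 7.07 | 7.45 | +0.38 |
| Control 80% then 10%; intervention 90% then 20% | 7.12 | 6.99 | −0.13 |
| Height on day 1 or never (50% vs 90%) | 6.85 | 6.85 | 0 |

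**5. Range when control heights are later.** With median stay 4 to 5 days, log-SD 0.7 to 0.9, control 30–70% on day 1 then 5–20% per day, and intervention 90% then 20%, the spurious difference runs up to about −1.5 days. A second set of assumptions used shifted exponential or lognormal stay, early height in 80–90% of intervention and 20–60% of control children, and later delays averaging 3 days (intervention) or 3–6 days (control). It gives −0.1 to −1.1 days (−2% to −12%), and zero when timing is the same in both arms. Cost was not simulated; it would follow through its dependence on stay.

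**6. When height timing depends on stay.** Take setting A, but let longer-stay children be less often measured on day 1 (log-odds −0.5 per SD of log stay). All screened: 7.34 (control) vs 6.93 (intervention), or −0.41. Height by day 2: 5.89 vs 6.60, or +0.71. Here the restriction makes the bias larger and reverses it.

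**The case against.** A reader might infer that the trial will show a falsely shorter stay in the intervention arm. The documents do not support that, for four reasons.

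- **Direction.** Training and mandatory measurement may turn late heights into early ones, but may also turn never-measured children into late-measured ones. The first favours the intervention; the second works against it (setting B).
- **Timing.** The Participants section speaks of ratios on entry and measurements at admission. Day 15 is an outer limit, and late heights may be few. The measurement rule came from hospital-level boards. The control section withholds the leadership strategy from control wards, but how far the rule reached them is open.
- **Precision.** With the protocol's ICC of 0.05 and 200 children per cluster, the design effect is 1 + 199 × 0.05 = 10.95. With 600 children per arm and an assumed SD of 6.7 days, the standard error of the difference is √(2 × 6.7² × 10.95 / 600) = 1.28 days. A 0.7-day artefact is about half of that. Only secondary outcomes are at issue here.
- **Remedy.** Restricting to height by day 2 is itself selection on something the intervention changes, and step 6 shows that it can do harm.

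The first three points stand as limits on size and direction. They do not remove the mechanism, since a 15-day window matters precisely when late heights occur. The fourth stands against replacing the main analysis set. It may also be said that landmark and sensitivity sets belong in an analysis plan. That is fair, but the entry window and the outcome are fixed here, and together they create the problem.

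**Conclusion.** The point holds in conditional form. As written, the entry rule and the whole-stay outcomes can produce a difference in mean length and cost of stay, between arms or between periods in the intervention arm, with no true effect. No listed covariate corrects it.

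If control heights are mainly later, the bias favours the intervention, by about 0.1 to 1.5 days under the assumed inputs. If unmeasured control children mostly stay unmeasured, it is zero or reversed. Neither size nor direction can be derived from the document, which gives no stay or height-timing data. That the stay is counted from admission is an inference from the claims source and from Table 1 timing eligibility from admission; it is not stated outright. This is worth correcting for these secondary outcomes; nothing here shows an effect on the primary ones.

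**What to change.** 1. Report the day of first height and the proportion of children measured, by arm and by period.
2. For length and cost of stay, pre-specify beside the all-screened analysis a day-2 landmark analysis, limited to children with both height and weight recorded by day 2.
3. For length of stay, add a delayed-entry (left-truncated) analysis in which each child enters on the day both measurements exist. This is not proposed for cost, since no daily costs are described.
4. Apply the same analyses to the pre/post comparison.
5. Claim a shorter or cheaper stay only if the analyses agree.

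The cost is analysis work only: the date of first height is already needed to apply Table 1, and the Time frame section says the statistical work is still under way. The downside is fewer children, mainly control, in the day-2 set. Both added analyses also assume that height timing is unrelated to prognosis for stay. Where it is related, the day-2 restriction can bias the comparison, so it should stand beside the main analysis set and not replace it.
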